### Outcomes

The primary outcome is feasibility. The proportion of HIV-positive, pregnant women who are approached and screened but do not meet eligibility criteria will be recorded, as well as the proportion of women who meet eligibility criteria but decline to participate. Data will be collected on the gestational age at screening and enrollment. Data will also be collected on the reasons for non-participation. This information will be used to determine the number of centers that will be required for timely recruitment of a larger randomized control trial (RCT). A consent rate of less than 60 % among women that meet eligibility criteria would be grounds for not moving forward with a larger RCT in this setting.

Secondary outcomes include safety, acceptability, compliance, and barriers to adherence. Safety and tolerability will be assessed through questionnaires administered to participants during the study, and by recording adverse events (AE) using the Division of AIDS (DAIDS) Table for Grading the Severity of Adult and Pediatric AEs and Addendum 1 Female Genital Grading Table for Use in Microbicide Studies [48]. AEs of all grades will be recorded, and the proportion of participants who report AEs will be compared between study arms. Any grade 4 AE or severe adverse event (SAE) attributed to progesterone supplementation would be grounds for not moving forward with a larger RCT. Standardized questions will capture group A’s experience with progesterone self-administration and information on local irritation or discomfort. Study acceptability will be measured by capturing whether participants are willing to be randomized to the no intervention arm, and participants’ overall impression of the study. Compliance to treatment will be assessed in group A via capsule count and through a standardized compliance questionnaire at each follow-up visit. Barriers to adherence to progesterone supplementation, and to study follow-up visits, will be assessed using standardized questionnaires.

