### Treatment allocation, randomization, and blinding

Participants who consent to the study will be randomized in a 5:3 fashion into two open-label arms: group A (treatment arm) or group B (no-treatment arm). The allocation sequence will be generated in advance by a statistician. Upon obtaining informed consent, study personnel will log into the web-based program to determine the participant’s treatment assignment.

While the participant and the treating physician will not be blinded, the laboratory personnel performing the biochemical and morphological evaluations will be blinded ensuring unbiased evaluation. Study outcomes such as birth weight and gestational age are also objective measures.

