### Participant timeline and monitoring

Every participant will be screened and enrolment will occur between GW16 to GW24. The rationale for this study initiation range is threefold: (1) it enables us to capture a larger group of eligible women, (2) it permits progesterone exposure during the time period where most fetal growth occurs (late second and third trimesters), and (3) it omits progesterone exposure during the first trimester where increased risk for hypospadias has been reported [49]. Participants will be followed monthly during their pregnancy, at delivery, and until their exit visit at 4 to 8 weeks post-delivery. During this time, information will be collected from participants’ routine blood work, urine sampling, and prenatal ultrasounds conducted as per standard of care.

During the screening visit, the study is introduced and consent is sought if the woman meets study inclusion and exclusion criteria. A screening log is kept, and the demographics of eligible participants who do not consent to the study are collected. Study personnel collect information on the reasons why a potential participant may have declined participation. Eligible women at less than 16 weeks gestation are screened, but consent and enrollment are deferred to GW16.

For the baseline visit, women undergo a full physical examination. Additional blood and urine samples are collected for assessing progesterone levels and meeting exploratory objectives (i.e., analyzing PI drug concentrations, sex steroids, angiogenic, vasoactive, and inflammatory factors and factors associated with placentation, placenta dysfunction, preterm delivery, and fetal growth restriction). Similar blood and urine sample collection occurs at 1 week after the baseline visit, at GW25–GW28, and at GW33–GW36. During the baseline visit, demographics and relevant medical history are collected by chart review and from the participant as required. Participants are then randomized into either group A or group B. After being appropriately educated on how to self-administer progesterone capsules intravaginally, participants in group A begin progesterone supplementation (administered as two capsules of Prometrium 100 mg) nightly from GW16–GW24 until GW36.

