### Statistical analysis

The primary endpoint is the proportion of enrolled participants out of all eligible patients. Qualitative information on the reasons to decline participation will be collected and summarized.

Secondary endpoints include the safety of progesterone supplementation during pregnancy for HIV-positive women as measured by the frequency and severity of AEs in group A and group B. Compliance to progesterone supplementation will be assessed in group A by the proportion of missed doses out of the total prescribed doses per participant. The acceptability of the intervention and barriers to adherence to progesterone supplementation will be recorded for participants in group A. For both group A and B participants, barriers to appointment attendance will be captured and acceptability of the entire study will be assessed in an exit questionnaire.

The relationships between progesterone levels (serum or urine) at baseline, 1 week post-baseline, GW25–GW28 or GW33–GW36 and birth weight, birth weight percentile, and gestational age at birth will be assessed with Spearman’s rank correlation. Serum/urine progesterone levels will be compared between women with and without an AE/SAE using descriptive statistics, if sufficient numbers of events occur. The levels of biomarkers will be compared between the two arms at baseline, 1 week post-baseline, GW25–GW28, GW33–GW36 and delivery visits using descriptive statistics and graphical methods. Qualitative assessment of placenta morphology will be performed blinded to the arm allocation and birth outcome.

Although, this pilot study is not powered for subgroup analyses, qualitative assessment of the impact of race, age, previous adverse pregnancy outcome on enrollment into study, acceptability of progesterone, and adherence will be conducted where possible.

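### Willingness to be randomised to no intervention, one component of study acceptability, is close to 100% by design if measured in enrolled women

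*Protocol article*

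**What the plan says.** The Outcomes section of the protocol article lists acceptability among the secondary outcomes. Its first component is "Study acceptability will be measured by capturing whether participants are willing to be randomized to the no intervention arm", and the sentence goes on to a second: "and participants’ overall impression of the study". The Statistical analysis section adds that, for women in groups A and B, "acceptability of the entire study will be assessed in an exit questionnaire".

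On entry, the section on treatment allocation states: "Participants who consent to the study will be randomized in a 5:3 fashion into two open-label arms". It also fixes the order of events: "Upon obtaining informed consent, study personnel will log into the web-based program to determine the participant’s treatment assignment".

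For women who decline, the section on participant timeline and monitoring describes a screening log in which "the demographics of eligible participants who do not consent to the study are collected". It adds: "Study personnel collect information on the reasons why a potential participant may have declined participation". The same section describes the collection of relevant medical history only at the baseline visit, which takes place after consent.

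The Statistical analysis section also plans a qualitative look at the effect of race, age and "previous adverse pregnancy outcome on enrollment into study, acceptability of progesterone, and adherence will be conducted where possible".

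**The concern.** A woman who has agreed to be randomised 5:3 between progesterone and nothing has, by that act, accepted the chance of receiving nothing. Asking her afterwards whether she is willing to be randomised to the no-intervention arm returns her entry condition. The women for whom that arm is unacceptable are among the decliners, and a measure taken in enrolled women does not reach them.

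What is at stake is modest but real. The pilot exists to inform a larger trial. A willingness figure near 100% could be read as evidence that the no-treatment arm is well accepted, when it shows only that consenting women consented.

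A smaller, related point concerns the enrolment assessment. To see whether previous adverse pregnancy outcome affects enrolment, that history is needed for decliners as well as enrolled women. The article states only demographics and reasons for decliners.

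**Working it through.** **1. Inputs.** From the article: 40 women to be randomised, allocation 5:3, and a consent rate below 60% of eligible women as grounds for not proceeding. Assumed, because the article gives no expected figures: the consent rate actually reached, and how the reasons for declining divide.

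**2. The plan's own figure.** 40 × 5/8 = 25 and 40 × 3/8 = 15. This reproduces the arm sizes in the abstract, which are not in dispute.

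**3. The item among enrolled women.** Consent precedes allocation, and only consenting women are allocated. Willingness is therefore 40/40 = 100% by construction. An exact (Clopper-Pearson) 95% interval would have the lower limit 0.025^(1/40) = 91.2%. That interval looks precise but says nothing about eligible women as a whole.

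**4. How many women fall outside the measure.** Eligible women = 40 / consent rate; decliners = eligible − 40. If every decliner refused because of the no-treatment arm, willingness among eligible women would be at its lowest, 40 / eligible. If none did, it would be 100%.

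| Assumed consent rate | Eligible | Decliners | Possible willingness among eligible women | Item among enrolled women |
|---|---|---|---|---|
| 50% | 80 | 40 | 50% to 100% | 100% |
| 60% | 67 | 27 | 60% to 100% | 100% |
| 70% | 57 | 17 | 70% to 100% | 100% |
| 80% | 50 | 10 | 80% to 100% | 100% |
| 90% | 44 | 4 | 91% to 100% | 100% |

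The last column does not move with the fourth. At 60%, the lower end is 40/67, with an exact 95% interval of 47% to 72%.

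**5. One illustration inside that range.** Take 67 eligible women and suppose that 15 of the 27 decliners refuse because of the no-treatment arm, while the other 12 refuse for unrelated reasons and would have accepted it. Willingness among eligible women is then (40 + 12)/67 = 52/67 = 78%, against 40/40 = 100% as measured. The split of 15 and 12 is assumed.

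**6. The enrolment assessment.** Each factor set against its stated source among decliners:
- Age: the demographics on the screening log.
- Race: presumably the same demographics, although the items are not listed.
- Previous adverse pregnancy outcome: no source stated, since medical history is described only at the baseline visit.

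**The case against.** The strongest reply is that the outcome is wider than the one item. That stands. The overall impression of the study and the exit questionnaire can both vary among enrolled women. A reader might infer from the first component that study acceptability as a whole cannot vary; the documents do not support that.

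A second reply is that the article uses the word participants loosely. It speaks of eligible participants who do not consent, so the item might be meant for all women approached. This is possible, but the context points the other way. The Outcomes section describes decliners separately, as women who meet the criteria but decline, and the Statistical analysis section places study acceptability with groups A and B. On the wider reading the text would still need a denominator and a time of asking.

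A third reply is that reasons for declining are already collected, so objections to the no-treatment arm can surface there. This stands in part, and it means decliners are not ignored. But the reasons are to be summarised qualitatively and are not linked to the acceptability outcome. Nor does the article say that each eligible woman is asked about this arm, so no proportion willing follows.

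Two further inferences should be resisted. One is that the pilot fails to settle whether the larger trial needs a placebo; the article does not pose that question. The other is that the whole enrolment assessment lacks data on decliners. Their demographics are collected, the assessment is qualitative and planned only where possible, and log fields may be set out in the full protocol.

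**Conclusion.** The point holds for one component of one secondary outcome. Read in its context, willingness to be randomised to no intervention is measured in women who have already accepted it, and will be at or near 100% whatever eligible women as a whole think. It is essentially rather than strictly fixed: a woman might answer differently in hindsight, but that would measure satisfaction after allocation.

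The gap between the item and willingness among eligible women depends on the consent rate and on why women decline. At the 60% threshold it could be anything from nothing to 40 percentage points; the 78% against 100% is an illustration within that range, not an estimate. The primary endpoint and the consent-rate rule are unaffected, as are the parts of acceptability that rest on overall impression and the exit questionnaire. The missing source for previous adverse pregnancy outcome among decliners is a minor note.

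**What to change.** Record willingness to be assigned to no intervention for every eligible woman approached, at the consent decision, on the existing screening log. It can be a direct coded question or a coded reason for declining. Report it with all eligible women approached as the denominator, and state how many did not answer. Keep overall impression and the exit questionnaire as they are.

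For the enrolment assessment, either add one yes/no field for previous adverse pregnancy outcome to the decliner log, subject to the ethics board's agreement, or limit that assessment to age and race.

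The cost is a few log fields and a minor notification to the ethics board. Some decliners will not answer, so the result should be shown with its non-response.

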### Declining progesterone levels as a potential mechanism for the impact of protease inhibitors on birth outcomes

We have previously reported experimental findings demonstrating that PI use during pregnancy is associated with decreased progesterone levels that correlate with fetal growth, and that progesterone supplementation can improve PI-induced fetal growth restriction [40]. Exposure of a human placental cell line to PIs (atazanavir, lopinavir, ritonavir), but not nucleoside reverse transcriptase inhibitors (NRTIs; zidovudine, lamivudine) or a non-NRTI (NNRTI; nevirapine), resulted in decreased progesterone production. In an animal model of pregnancy, lower progesterone levels were detected in mice exposed to PI-based cART (ritonavir-boosted lopinavir) but not in those exposed only to the NRTI backbone. Moreover, the change in progesterone levels was associated with smaller fetuses and other adverse birth outcomes. To establish a direct relationship between progesterone levels and birth outcomes, PI-based cART exposed mice were supplemented with natural progesterone throughout their pregnancy. Progesterone supplementation significantly increased fetal weight in these mice.

Consistent with these data, we have also observed lower progesterone levels at gestational weeks 25–28 in HIV-positive pregnant women exposed to PI-based cART compared to HIV-negative pregnant women. Progesterone levels in the HIV-positive women were significantly correlated with birth weight percentile [40].

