Exploratory outcomes include (a) changes in serum/urine progesterone levels during pregnancy, (b) correlation of serum/urine progesterone levels with birth weight, birth weight percentile, and gestational age at birth, (c) the relationship between degree of adherence to progesterone supplementation with birth weight, birth weight percentile, and gestational age at birth, (d) the distributions of birth weight and gestational age at birth, including low birth weight (< 2500 g) and small for gestational age births, (e) serum and cell levels of sex steroids, angiogenic, vasoactive, and inflammatory factors, and factors associated with placentation, placenta dysfunction, preterm delivery, and fetal growth restriction, (e) placenta histology, and (f) serum PI drug concentrations.

This study will also provide information on the standard deviation of the change in progesterone levels, and the intra-patient correlation coefficient among repeated progesterone levels during pregnancy to inform the design of a larger RCT.

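### The baseline and 1-week progesterone correlations with birth outcomes make no allowance for gestational age at the draw, which varies by about 8 weeks (low severity, exploratory analysis)

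*Protocol article*

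**What the plan says.** All places are in the protocol article.

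- **Outcomes.** Exploratory outcome (b) is the "correlation of serum/urine progesterone levels with birth weight, birth weight percentile, and gestational age at birth". Exploratory outcome (a) is change in progesterone during pregnancy. The same section says that gestational age at screening and at enrolment will be recorded.
- **Participant timeline and monitoring.** "Every participant will be screened and enrolment will occur between GW16 to GW24". The first study samples are taken at the baseline visit. After that, "Similar blood and urine sample collection occurs at 1 week after the baseline visit, at GW25–GW28, and at GW33–GW36". Women seen early wait: "Eligible women at less than 16 weeks gestation are screened, but consent and enrollment are deferred to GW16".
- **Statistical analysis.** "The relationships between progesterone levels (serum or urine) at baseline, 1 week post-baseline, GW25–GW28 or GW33–GW36" and the three birth outcomes are to be assessed by Spearman's rank correlation. No covariate, stratification or standardisation for gestational age at the draw is named, and nothing is said about pooling or separating the arms.

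**The concern.** The last two draws are anchored to gestational windows. The first two are anchored to enrolment, so at one nominal visit some women are sampled at GW16 and others at GW24. A rank correlation at that visit is meant to order women by progesterone status. If the level moves with gestation, it also orders them by time of sampling. Birth weight percentile allows for gestational age on the outcome side; nothing does so on the exposure side.

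Two consequences differ in kind. If time of sampling is unrelated to birth outcome, the extra spread only pulls the correlation toward zero. If the two are related, the correlation is also biased. The deferral rule means that sampling time is not random, although the article does not say how it relates to outcome.

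The baseline level is of interest because it is the only one free of administered progesterone in both arms. A weak baseline correlation under the stated method would be hard to read: it could mean no association, or mixed sampling times.

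From 1 week on there is a second mixture: group A levels include administered progesterone while group B levels do not.

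**Working it through.** **The plan's own figures.** There is none to reproduce for these correlations. The 40 is a feasibility number with no power, alpha or target correlation. The split checks: 40 × 5/8 = 25 and 40 × 3/8 = 15.

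**Inputs from the article.** Baseline draw GW16–24; second draw one week later, GW17–25; n = 40; Spearman correlation with no covariate named.

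**Inputs assumed, because the article gives none.** Between-woman SD of log progesterone at fixed gestational age 0.30; rise of 3%, 5% or 8% per week; true correlation 0.40 at fixed gestational age; correlation g between gestational age at the draw and birth outcome of 0 or -0.2; draw times uniform over W weeks. W = 8 if the window closes at 24 weeks 0 days, and about 9 if all of week 24 counts.

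**Step 1: share of the level due to sampling time.** Express the slope in between-woman SDs: 0.03/0.30 = 0.10, 0.05/0.30 = 0.167 and 0.08/0.30 = 0.267 per week. A uniform window has SD W/√12, which is 2.31 weeks for W = 8 and 2.60 for W = 9. Let k = slope × SD of draw time. The share of variance is k²/(1 + k²).

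- W = 9: k = 0.260, 0.433, 0.693, so the share is 6%, 16%, 32%.
- W = 8: k = 0.231, 0.385, 0.616, so the share is 5%, 13%, 28%.

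For comparison, in the GW25–28 window (taken as 3 weeks) slopes of 0.05 to 0.3 SD per week give only 0.2% to 6%.

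**Step 2: effect on the correlation.** Without adjustment, the expected Pearson correlation is r = (0.40 + g·k)/√(1 + k²). The approximate Spearman value is (6/π)·arcsin(r/2). At fixed gestational age, 0.40 becomes 0.385 in large samples, and about 0.375 on average at n = 40.

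Worked for W = 9 and 8% per week:
- g = 0: r = 0.40/√1.480 = 0.329, Spearman 0.315.
- g = -0.2: r = (0.40 - 0.139)/1.217 = 0.215, Spearman 0.206.

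**Step 3: simulation at n = 40, W = 9 (1,500 runs per scenario).**

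| Rise per week | g = 0, unadjusted | g = -0.2, unadjusted | Adjusted |
|---|---|---|---|
| 3% | 0.37 | 0.31 | about 0.375 |
| 5% | 0.34 | 0.26 | about 0.375 |
| 8% | 0.30 | 0.20 | about 0.375 |

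A repeat with 3,000 runs agreed to within 0.01. With no true association, 5% per week and g = -0.2, the unadjusted value averages about -0.07 instead of 0; the formula gives -0.076. With W = 8 and g = 0, the unadjusted values are 0.37, 0.35 and 0.31.

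**Step 4: scale.** At n = 40 the standard error of a correlation near 0.375 is roughly (1 - 0.375²)/√37 = 0.14. The attenuation alone (at most about 0.07) is smaller than that. The loss in the worst scenario (0.375 - 0.20 = 0.175) is larger.

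**Step 5: cost when nothing is wrong.** With no weekly trend, the unadjusted and adjusted values agree at 0.38.

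**The case against.** **Importance.** This is an exploratory analysis in a feasibility pilot. The stated no-go rules are a consent rate below 60% and an attributable grade 4 or serious adverse event. What passes to the larger trial is the standard deviation and intra-patient correlation of progesterone, not these correlations. This stands, and it keeps the severity low.

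**Silence.** The article condenses a longer protocol, so an adjustment might be specified elsewhere, and that the levels are unadjusted is an inference. This stands in part. But the article does fix the exposure, the times, the outcomes and the method, and two of the times are not tied to gestation. Improving that stated choice is more than asking for missing detail.

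**Size.** Every figure above rests on assumed slopes and links. At 3% per week with no link there is no practical effect. This stands.

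**Other analyses.** Correlations at GW25–28 and GW33–36 are already planned and suffer much less from this. That is so, but those levels carry administered progesterone in group A.

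**Stronger readings that a reader might infer and the article does not support:**
- *That the team's earlier correlation came from a fixed 4-week window.* The Background says "we have also observed lower progesterone levels at gestational weeks" 25–28, but of a comparison with HIV-negative women. The sentence on the correlation with birth weight percentile states no window.
- *That a late draw marks a late presenter.* A woman who starts or switches to a protease inhibitor regimen later, or is referred later, is also sampled late.
- *That late enrolment goes with smaller babies, so that the result is biased toward or below zero.* The article says nothing on this; without such a link there is attenuation only.
- *That baseline gives a clean test in all 40 women.* Afterwards 25 of them receive a treatment hypothesised to affect birth outcome, and women only starting a protease inhibitor may have had little exposure by then.

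**Conclusion.** The point holds as a low-severity improvement to an exploratory analysis. The baseline and 1-week draws follow enrolment, and the stated correlation makes no allowance for gestational age at the draw. If progesterone changes over GW16–25, which exploratory outcome (a) contemplates, the ranks mix progesterone status with sampling time.

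The certain part is the direction of the simple effect: attenuation whenever there is a trend. Bias beyond that needs a relation between timing of enrolment and birth outcome, which the article neither states nor excludes. The magnitude is conditional on the assumptions listed and cannot be narrowed from the article. It does not bear on the primary feasibility outcome or on whether a larger trial proceeds.

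**What to change.** Amend the sentence on Spearman correlation in the Statistical analysis section:

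- **Baseline sample:** use a Spearman correlation partial on gestational age at the draw, in days.
- **1-week, GW25–28 and GW33–36 samples:** use a Spearman correlation partial on gestational age at the draw and on study arm, or report the correlations by arm. Adjusting for gestational age alone would leave administered progesterone in group A mixed into the ranks.

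The unadjusted correlations can be kept alongside for description. Gestational age at enrolment is already recorded, and the sample dates give the rest, so no new data are needed. The cost is one degree of freedom at baseline and two at later draws. Reporting by arm instead leaves 25 and 15 women per correlation, so those estimates will be less precise.
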